### Study stopping rules

The study will be temporarily paused to review safety data if any of the following study stopping rules are met:More than 1% of the enrolled infants have an inpatient seizure, as assessed on a rolling basis, and the total number of cases equaling 7 or more.More than 35% of the enrolled infants who were pharmacologically treated have an outpatient acute/urgent care or emergency room visit, as assessed on a rolling basis, and the total number of cases equaling 252 or more.More than 10% of the enrolled infants who were pharmacologically treated have an outpatient hospital readmission, as assessed on a rolling basis, and the total number of cases equaling 72 or more.

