## Abstract

**Background:**

Opioid use and misuse during pregnancy rose from 1.5 to 6.5 per 1000 deliveries between 1999 and 2014 and continues as a significant public health concern. A fivefold increase in neonatal opioid withdrawal syndrome (NOWS) has accompanied the increase in opioid use. The Eating, Sleeping, Consoling care approach (ESC) has been shown to improve outcomes for infants with NOWS and is quickly becoming the standard of care for infants affected by opioid use disorder. Quality improvement initiatives following the implementation of ESC provide some evidence to suggest that symptom-based (i.e., as needed, PRN, just in time) dosing of opioid medications for infants with significant withdrawal may be an effective alternative to using a traditional scheduled opioid taper approach. These initiatives have shown reduced length of hospital stay and decreased postnatal opioid exposure when compared to scheduled opioid dosing for infants with NOWS who receive pharmacologic treatment. It is unknown if the findings from these quality improvement initiatives are generalizable, and little is known about the safety of this approach in a diverse population. The purpose of this manuscript is to describe the design and rationale for an ongoing study to evaluate the effect of symptom-based opioid dosing compared to traditional scheduled opioid taper on short-term outcomes for infants with NOWS.

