#### Rational for selection of study intervention

The overarching hypothesis to be tested is if the use of a symptom-based dosing approach will lead to a reduction in the time until infants are medically ready for discharge when compared to a scheduled opioid taper approach. In the scheduled opioid taper approach, all patients who reach a symptom threshold will be treated with a study site’s usual pharmacologic treatment algorithm. Each algorithm is responsive to symptom severity to allow dosing escalation. All infants follow a protocolized weaning of opioid dose as prescribed by a study site’s pharmacologic treatment algorithm. The theoretic advantage of this approach is that infants with uncontrolled symptoms have a rapid dose escalation with rapid control of NOWS symptoms. The potential disadvantage is that infants are shunted into a treatment approach with denser opioid treatment than they may require for optimal symptom control, with an associated prolongation of hospital stay. The symptom-based approach allows for up to three individual doses in any 24-h period before beginning a scheduled dosing protocol. The theoretic advantage to this approach is that one to three single doses may be enough to control symptoms without requiring a fixed and prolonged regimen. A potential disadvantage is that this approach may delay the start of scheduled opioid dosing in some infants, which may ultimately increase the duration of hospitalization. It is also unclear if the number of infants treated, as defined as receipt of a single dose of opioid, will differ between the two groups. Quality improvement work suggests that clinicians may be more likely to give a single dose for infants with less severe symptoms rather than waiting until symptoms meet the typical thresholds for the initiation of an opioid taper, possibly leading to a greater proportion of infants treated at study sites using a symptom-based protocol.

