An evidence-based choice of optimal secondary medication is also not defined in the literature. Though doses are largely empirically derived, extrapolated from adults, or in the case of phenobarbital extrapolated from use in seizure control, there is a greater convergence upon a more standardized dose regimen than with opioids. All study sites will adhere to the following broad dosing parameters (Table 2).

**Table 2 Tab2:** Secondary and tertiary medication dosing parameters [15]

	Phenobarbital	Clonidine
Maximum loading dose	20 mg/kg	N/A
Minimum initial dose	1.25 mg/kg/day	0.625 mcg/kg
Maximum daily dose	5 mg/kg/day	24 mcg/kg/day

All enrolled infants will be assessed at 3 months of age for the use of nonscheduled medical care which includes acute/urgent care visits, emergency room visits, and hospital readmissions. This assessment will include a review of the medical records which will include data from the hospital in which the infant was born, and any additional information that can be assessed through linked medical records.

All enrolled infants will be assessed for seizures and death until hospital discharge.

All enrolled infants will also be assessed for non-accidental trauma or death at 3 months of age. These assessments will include a review of the medical records including data from the hospital in which the infant was born, and any additional information that can be assessed through linked medical records, in addition to a review of public facing media.

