### Data collection methods

Data collected will be from the infant and maternal medical records, including transfer records. All clinical data collected from this study will be extracted directly from the electronic health records or source documents. There will be no interactions with, nor will there be any information collected directly from, the mother, the infant, or the treating clinician.

The site research team will assess the outpatient composite safety outcome as well as the outpatient critical safety outcome through review of the medical records (including the study site’s primary and any linked electronic medical record systems) and media review (public facing) for all enrolled infants at approximately 3 months of age.

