### Analysis populations

The following analysis populations will include all randomized study sites that enrolled participants, regardless of the degree of adherence to the study interventions.

Intention-to-treat population (ITT): All enrolled participants at a study site during the study. Each participant will be analyzed according to the study intervention that the study site was assigned at the time the participant was born.

Intention-to-treat population—pharmacologically treated (ITT-PT): All participants in the ITT population who were pharmacologically treated at a study site during the study. Each participant will be analyzed according to the study intervention that the study site was assigned at the time the participant was born.

Intention-to-treat population—pharmacologically treated with symptom-based dosing approach (ITT-PT1): All participants included in the ITT-PT population who were pharmacologically treated using a symptom-based dosing approach.

Intention-to-treat population—pharmacologically treated with scheduled opioid taper approach (ITT-PT2): All participants included in the ITT-PT population who were pharmacologically treated using a scheduled opioid taper approach.

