If 2 participants are accrued per site per month across the 24 sites, a total sample size of 480 participants would require 5 months per period. The duration of each period is expected to be 5 months; this length may need to be modified to ensure sample size is met in Finnegan and ESC groups. Additionally, due to variation in enrollment across the sites and that enrollment in each period will end at the same time across all sites, the number of infants enrolled in the study may be higher than 480.

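### At the planned 480 infants the seizure pause rule is insensitive: its 7-case floor fits about 700–720 infants, and pooling the two dosing approaches weakens it further.

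*Protocol article*

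**What the plan says.** The Study stopping rules section of the protocol article sets three triggers for a temporary pause. The seizure trigger is met when "More than 1% of the enrolled infants have an inpatient seizure, as assessed on a rolling basis" and, as a second condition, "the total number of cases equaling 7 or more". Numerator and denominator are all enrolled infants, with no split by dosing approach. The two outpatient triggers, counted among treated infants, have floors of 252 cases at 35% and 72 cases at 10%.

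The Abstract gives 480 infants as a minimum. Sample size considerations builds that figure from 24 sites and adds that "the number of infants enrolled in the study may be higher than 480", without an upper figure. Sites are randomized 1:1 to two sequences and each site uses both approaches, so about half the infants fall under each.

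On timing, the Dosing parameters section states: "All enrolled infants will be assessed for seizures and death until hospital discharge". The DSMB sees safety summaries every 3–6 months (Interim analysis of safety data) and again with the interim efficacy analysis.

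**The concern.** A rolling pause rule is meant to act between scheduled DSMB reviews. Here those reviews may be 3–6 months apart, while each treatment period is expected to last 5 months. Seizures suit such a rule because they are known before discharge.

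Two features blunt it. The count floor looks sized for a larger trial, so at 480 infants the 1% condition never decides anything. The count also ignores which approach the infant was under, although the trial compares two approaches and the Abstract says of symptom-based dosing that "little is known about the safety of this approach in a diverse population". A real excess of seizures under one approach could run through most of enrolment without triggering a pause.

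**Working it through.** **Inputs.** From the article: limit 1%, floor 7, sister floors 72 at 10% and 252 at 35%, planned 480 infants, roughly 1:1 split. Assumed, because the article gives no seizure rate: background rate b of 0–0.3% in the unaffected approach, and the true rates used in the simulations.

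**Which trial size do the floors fit?** 7/0.01 = 700; 72/0.10 = 720; 252/0.35 = 720; and 1% × 720 = 7.2. For the planned size, 1% × 480 = 4.8, which rounds up to 5. The article does not state 720; it is inferred from the floors.

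**What the full rule needs.** Cases needed: c = the larger of 7 and the smallest whole number above 0.01N. Pooled rate at a pause = c/N. With a 1:1 split, the rate in the affected approach is s = 2c/N − b.

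| N | c | Pooled rate | s, b = 0 | s, b = 0.1% | s, b = 0.3% |
|---|---|---|---|---|---|
| 480 | 7 | 1.46% | 2.92% | 2.82% | 2.62% |
| 600 | 7 | 1.17% | 2.33% | 2.23% | 2.03% |
| 699 | 7 | 1.00% | 2.00% | 1.90% | 1.70% |
| 720 | 8 | 1.11% | 2.22% | 2.12% | 1.92% |

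Below 700 infants, 7 cases always exceed 1%, so the rule reduces to a count of 7.

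**Chance of a pause.** Simulated trials (20,000–40,000 per scenario), infants alternating between approaches, rule checked after every infant, no site clustering. Repeat runs agree to within 1–2 percentage points.

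| 480 infants | 2% v 0.3% | 1.5% v 0.3% | 0.5% in both |
|---|---|---|---|
| Written rule | 32% | 15% | 1.1% |
| Written rule plus by-approach (>1%, ≥5) | 54% | 30% | 2.0% |
| Pooled floor 5 | 65% | 43% | 9.3% |
| By-approach (>1%, ≥4) alone | 71% | 48% | 6.5% |
| Pooled floor 5 plus by-approach ≥4 | 74% | 52% | 10.9% |

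| 720 infants | 2% v 0.3% | 1.5% v 0.3% | 0.5% in both |
|---|---|---|---|
| Written rule | 70% | 44% | about 6% |
| Written rule plus by-approach (>1%, ≥5) | 86% | 64% | about 9% |

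**Separating floor from pooling (2% v 0.3%).**
- At 480, splitting by approach but keeping the floor at 7 lowers detection from 32% to 21%. Lowering the pooled floor to 5 raises it to 65%, and adding a by-approach floor of 4 gives 74%. The floor thus accounts for 65 − 32 = 33 points and the split for a further 74 − 65 = 9.
- At 720, a pooled floor of 5 alone gives 78%, and adding a by-approach floor of 5 gives 87%. About half of the rise from 70% to 86% is therefore also a floor effect; the split itself is worth about 87 − 78 = 9 points.

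**Harm common to both approaches (1.5% in each, 480 infants).** Pooled floor 5: 85%; by-approach ≥4 alone: 73%; both: 86%. A pooled part should stay.

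**The case against.** The strongest reply is that this is a monitoring preference. Crossing the limit only pauses the trial. Seizures are adverse events of special interest, the DSMB reviews cumulative events, and displays by arm normally belong in its charter. A more sensitive rule also pauses more trials without cause. All of this stands and limits the weight. It does not explain a floor that matches neither 1% of 480 nor any enrolment figure in the article.

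It is also fair to say that pooling is not the main fault at 480. Under a count of 7, cases in the other approach help to reach the trigger, and a split at the same floor does worse. Nor does the safety question lie on one side only: the Study intervention section says neither approach has generalizable evidence of better safety. A by-approach trigger should therefore cover both.

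Three stronger readings are tempting, and the article does not support them:
- **A broken 1% promise per approach.** The 1% is stated only for all enrolled infants, so nothing is contradicted.
- **A one-approach threshold of 1.7–1.9%.** That is 2 × 1% − b for b of 0.1–0.3%. It ignores the case floor and fits the full rule only near 699 infants; at 480 it understates the rate needed.
- **By-approach floors for the outpatient triggers.** Their margins would need background rates that the article does not give, so they are no part of this point.

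**Conclusion.** The point holds as a weak design choice, of minor to moderate weight. At 480 infants the rule needs 1.46% overall, or about 2.6–2.9% in one approach. It would miss roughly two of three trials with true rates of 2% and 0.3%. The ill-fitting floor is the main cause; pooling adds a smaller loss, which gains in relative importance as enrolment approaches 720 and the floor comes into proportion.

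The thresholds rest on a 1:1 split and an assumed background rate of 0–0.3%. The detection figures also rest on assumed true rates and independent infants. A rougher run with site-level variation in risk (24 sites, assumed ICC 0.05, 2% v 0.3%, 480 infants) gave 33% for the written rule, 60% with pooled floor 5 and 69% with the by-approach floor of 4 added, so the ordering does not depend on independence. A reader might infer that seizure oversight fails altogether; it does not, since DSMB review every 3–6 months continues.

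**What to change.** **Least costly version.** Keep the written seizure rule and add: pause if, under either dosing approach, more than 1% of enrolled infants have an inpatient seizure with 5 or more cases. Assign infants as the Analysis populations section already does: "analyzed according to the study intervention that the study site was assigned at the time the participant was born".

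**More sensitive version.** Set the pooled floor to 5, to match 1% of 480, with or without a by-approach trigger at 4 or more cases. If about 720 infants are expected, keep 7 for the pooled part and 5 by approach. Keep a pooled part in every version.

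The DCC applies the rule and tells only the DSMB which part was met. The notice to sites should not name the approach, because a one-sided pause could signal the direction of results.

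**Cost.** Wording in the protocol and DSMB charter; no new data. The price is more needless temporary pauses. At 480 infants and an equal 0.5% risk they rise from 1.1% to 2.0% for the least costly version, and to about 11% for pooled floor 5 plus by-approach floor 4. With site variation (ICC 0.05) that last change is from 3.3% to 16.1%. At 720 infants the least costly version moves from about 6% to about 9%. The change helps only while infants are being enrolled; Trial status anticipated that enrolment would end in April 2025.

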### Sample size considerations

The primary objective will be addressed by separately testing the intervention effect in infants who were assessed and managed with ESC. Secondary objective #1 will be addressed by separately testing the intervention effect in infants who were assessed and managed with FNAST. Consequently, sample size calculations have been provided for both groups.

Given the population and study interventions under study, sample size was selected by defining a clinically meaningful effect size of a 15%–25% reduction in time to medically ready for discharge when comparing this endpoint in infants with NOWS who are assessed and managed with ESC and who are treated with a symptom-based dosing approach to infants with NOWS who are treated with a scheduled opioid taper approach. To ensure that the study is conducted in the same time frame across the 16 ESC and 8 FNAST sites, a similar sample size will also be used for FNAST sites, acknowledging that a clinically meaningful effect size of 15%–25% may not be detectable with sufficient statistical power due to the smaller number of FNAST sites selected for this study.

All sample size calculations were performed using the Shiny CRT Calculator: Power and Sample Size for Cluster Randomized Trials [26] with the following options:Sampling structure: cross-sectional sampleCorrelation structure: exchangeableAllowance for varying cluster sizes: noOutcome type: countNormal approximation: *T*-distribution

Note that using data obtained from INFORM NOW during the periods of October 1, 2019–December 31, 2019, and July 1, 2021–March 31, 2022, we observed that:349 infants met the eligibility criteria outlined in the Participant selection section and were assessed and managed with FNAST across 13 sites.◦ The mean time to medically ready for discharge was 16.35 days (95% CI: 12.97, 20.61) such that the estimated intra-class correlation coefficient was 0.1629 and the estimated over-dispersion parameter was 8.40.◦ 78.8% of participants received pharmacologic treatment.133 infants met the eligibility criteria outlined in the Participant selection section and were assessed and managed with ESC across 8 sites.◦ The mean time to medically ready for discharge was 10.46 days (95% CI: 8.02, 13.63) such that the estimated intra-class correlation coefficient was 0.1119 and the estimated over-dispersion parameter was 5.46.◦ 39.1% of participants received pharmacologic treatment.

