Assuming that the participants in OPTimize NOW are similar to those observed in INFORM NOW, sample size calculations of the primary endpoint given by time to medically ready for discharge were conducted under the following assumptions:In infants who were assessed and managed with FNAST:◦ The mean time to medically ready for discharge is approximately 16.50 in infants who are treated with a scheduled opioid taper approach.◦ Intra-class correlation coefficient in either arm is 0.15.◦ Over-dispersion parameter in either arm is 8.4.In infants who were assessed and managed with ESC:◦ The mean time to medically ready for discharge is approximately 10.50 in infants who are treated with a scheduled opioid taper approach.◦ Intra-class correlation coefficient in either arm is 0.15.◦ Over-dispersion parameter either arm is 5.5.

Under these assumptions, Table 5 shows that effect sizes that can be detected with 80% or 90% power in infants who are assessed and managed with ESC or FNAST using a total sample size of 480 participants (320 infants who are assessed and managed with ESC; 160 infants who are assessed and managed with FNAST) and assuming a two-sided significance level of 0.05. Specifically:In infants who are assessed and managed with ESC, a sample size of 320 will allow us to detect a relative rate in time to medically ready for discharge between infants who are treated with a symptom-based dosing approach versus infants who are treated with a scheduled opioid taper approach of 0.79 with 80% power and 0.76 with 90% power.In infants who are assessed and managed with FNAST, a sample size of 160 will allow us to detect a relative rate in time to medically ready for discharge between infants who are treated with a symptom-based dosing approach versus infants who are treated with a scheduled opioid taper approach of 0.71 with 80% power and 0.67 with 90% power.

**Table 5 Tab5:** Sample size calculations

Treatment approach	Number of sites per sequence	Number of infants with NOWS per site per period	Number of infants with NOWS	Power	Time to medically ready for discharge		Relative rate of days to medically ready for discharge between arms
					Scheduled opioid taper	Symptoms-based dosing	
ESC	8	10	320	80%	10.50	8.3	0.79
				90%		8.0	0.76
FNAST	4	10	160	80%	16.50	11.7	0.71
				90%		11.0	0.67

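### The minimum case counts in the two outpatient pause rules do not fit a trial of 480 infants, so the stated 35% and 10% limits do not govern

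*Protocol article*

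**What the plan says.** The section Study stopping rules gives three rules for a temporary pause. Each joins a percentage to a minimum count, and both must be met.

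- Seizures: "More than 1% of the enrolled infants have an inpatient seizure", with "the total number of cases equaling 7 or more". The denominator is all enrolled infants.
- Outpatient visits: "More than 35% of the enrolled infants who were pharmacologically treated have an outpatient acute/urgent care or emergency room visit". The denominator is treated infants only. The second condition for this rule reads "as assessed on a rolling basis, and the total number of cases equaling 252 or more".
- Readmissions: more than 10% of treated infants, with "the total number of cases equaling 72 or more".

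Sample size considerations bases its detectable effects on 320 ESC and 160 FNAST infants, "using a total sample size of 480 participants". The same section reports the treated share in the source cohort: for ESC, "39.1% of participants received pharmacologic treatment"; for FNAST, "78.8% of participants received pharmacologic treatment". It assumes that this trial's infants resemble that cohort. The abstract calls 480 a minimum, and the sample size section says enrolment may exceed it, without giving an upper figure.

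**The concern.** A minimum count beside a percentage normally stops a rule from firing on a handful of early events. Here the two outpatient counts are so large, relative to the number of infants who can contribute, that the count decides and the percentage has no effect. A reader of the protocol, a site or an ethics board would believe that a visit rate above 35% or a readmission rate above 10% in treated infants leads to a pause. As written, rates well above those limits would not.

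These are the only numerical safety-pause triggers in the article. The trial runs under waiver of consent, and the waiver justification points to DSMB oversight, so the written triggers should do what they say.

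**Working it through.** **Inputs.** Percentages 1%, 35%, 10% and counts 7, 252, 72 (Study stopping rules). Planned size 320 ESC + 160 FNAST = 480 and treated shares 0.391 and 0.788 (Sample size considerations).

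**1. Base implied by the stated counts** (count ÷ percentage).
- Visits: 252/0.35 = 720
- Readmissions: 72/0.10 = 720
- Seizures: 7/0.01 = 700, and 1% of 720 = 7.2, which rounds to 7

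A single base of 720 reproduces all three counts. The planned 480 does not. The same base also seems to serve for enrolled infants (seizures) and for treated infants (the other two rules); both could be 720 only if every infant were treated.

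**2. Treated infants expected at the planned size.**
320 × 0.391 + 160 × 0.788 = 125.1 + 126.1 = 251.2, or 52.3% of 480. Binomial variation alone gives about 231 to 271.

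**3. Rate needed before each rule can fire** (count ÷ denominator).
- Visits: 252/251.2 = 100.3%, stated 35%
- Readmissions: 72/251.2 = 28.7%, stated 10%
- Seizures: 7/480 = 1.46%, stated 1%

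**4. Chance that the readmission rule fires** (exact binomial, 251 treated, 72 or more cases).
- True rate 20%, twice the limit: 0.0006
- True rate 25%: 0.10
- True rate 30%: 0.70

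**5. Sensitivity to the number treated.**

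| Scenario | Treated | Visit rule needs | Readmission rule needs |
|---|---|---|---|
| 480 enrolled, planned mix | 251.2 | 100.3% | 28.7% |
| 480 enrolled, upper end of binomial range | 271 | 93.0% | 26.6% |
| 720 enrolled, same mix | 376.8 | 66.9% | 19.1% |
| 480 enrolled, every infant treated | 480 | 52.5% | 15.0% |
| 1,376 enrolled, same mix | 720 | 35.0% | 10.0% |

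Only the last row, 720/0.5233 ≈ 1,376 enrolled, makes the outpatient counts agree with their percentages.

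**6. Seizure rule.** With 480 enrolled, the probability of 7 or more cases is 0.85 at a true rate of 2% and 0.99 at 3%. This rule works.

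**7. Case numbers at which the stated percentages are first exceeded**, with 480 enrolled and 251 treated.
- Seizures: 0.01 × 480 = 4.8, so 5
- Visits: 0.35 × 251.2 = 87.9, so 88
- Readmissions: 0.10 × 251.2 = 25.1, so 26

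**The case against.** **480 is a floor and 251 is an expectation.** Periods may be lengthened, at least 24 sites are planned, and the rationale for the intervention allows that more infants may be treated under symptom-based dosing. This stands as far as it goes: a reader might infer that the visit rule can never fire, and the article does not support that. With 271 treated it could fire, at 93%. But no scenario near the plan brings the trigger close to 35% or 10%; even treating all 480 leaves 52.5% and 15%.

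**A minimum count is ordinary design.** True, and it clears the seizure rule. A reader might infer that all three rules fire far above their limits; for seizures the difference is 7 cases against 5, and at 720 enrolled 7 is 0.97%. It would also be wrong to say that such rules can fire only near full enrolment. At a true seizure rate of 3%, 7 cases are expected by about 7/0.03 = 233 infants. The defence fails for the outpatient rules, whose counts are large even against the full treated group.

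**The trial has other safeguards.** The DSMB reviews safety summaries every 3 to 6 months and again with the interim analysis (Interim analysis of safety data), and hospitalisations are collected as serious adverse events to 3 months of age (Collection of adverse event assessment and follow-up). This stands: high rates would probably be seen without the pause rules. It lessens the consequence but does not make the rules operate as stated.

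**The article is condensed.** The rules are printed with both percentage and count, so this is a stated figure that does not fit, not an omission.

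**Conclusion.** The counts of 252 and 72 are wrong for the trial as planned. At 480 enrolled the visit rule is practically inoperative (about 100% needed, 35% stated), and the readmission rule needs nearly three times its stated limit (28.7% against 10%). The seizure count is a minor mismatch.

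The result rests on the article's own treated shares carrying over, on the planned ESC and FNAST split, and on cases meaning infants with an event, as the percentages do. The binomial probabilities treat infants as independent; clustering by site would change them somewhat but not the required rates.

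A reader might infer that the trial was once planned at 720 and the counts were left behind. One base fitting all three counts is consistent with that, but the article nowhere says so, and the point does not depend on it. Nor do the documents support a claim that the trial lacks safety oversight.

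**What to change.** The study team and the DSMB should reconcile the counts, percentages and denominators in Study stopping rules with Sample size considerations, and re-derive the minimum counts from the enrolled and treated denominators. The percentages themselves are their decision.

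As arithmetic only, the stated percentages are first exceeded at 5 seizures, 88 infants with visits and 26 readmissions with 480 enrolled and 251 treated. Used as fixed minimums, these numbers would still override the percentages earlier on: at half the treated total, 251.2/2 = 125.6, a minimum of 26 means 26/125.6 = 20.7%. Any minimum should therefore be low enough that the stated percentages govern while the rules are applied on a rolling basis.

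The cost is wording in the protocol and in any DSMB charter that repeats the rules, plus a somewhat higher chance of a temporary pause. Sample size and data collection are unaffected.
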